**Power calculations:** The power calculation was conducted to estimate the sample size needed to test the primary hypothesis that participants receiving the NRT package will display significantly greater quit rates (30 day abstinence) at 6-month follow-up as compared to those not offered the NRT package. Our secondary analysis of the rural participants in our earlier trial indicated a large effect (OR = 9.59; 8.9% 30-day abstinence rate at 6 months in those receiving NRT vs 1% in those not receiving the intervention). However, this estimate is not stable due to the small sample size (n = 200 in participants from rural regions; 95% CI 1.19 to 77.16). As such, we have reduced the anticipated size of the impact of the intervention to 75% to generate the sample size estimate for the current proposal (i.e., OR = 7.1; 6.7% 30-day abstinence rate at 6 months in those receiving NRT vs 1% in those not receiving the intervention). This will allow for the likely possibility that, while the impact of the NRT intervention is large in rural regions, it may not be as large as was observed in the secondary analyses. The power analysis was based on Monte Carlo simulations. Randomly distributed dropouts were also included in the simulations, at a rate of 20%; thus accounting for the 20% attrition expected between baseline and 6-month post-intervention follow-up based on earlier trial findings. Quitting smoking was the binary outcome, measured as 30-days abstinence. A sample of 290 participants per group (intervention versus control) is needed in order to obtain 80% power with 95% confidence interval. Further, analyses from our earlier trial established that 50.1% of participants from rural regions would be interested in receiving nicotine patches (and would use it within a week to quit), leading to a baseline survey needed of 1,138 participants. Finally, results from our earlier trial found that 10% of those recruited at baseline were not eligible because of reporting a health condition

contraindicating NRT use without the supervision of a doctor. Thus, in order to conduct this trial, we would need to recruit 1,252 participants for the baseline survey in order to have sufficient participants for the trial (1,138 X 110%).

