**Analysis Plan:** Multilevel logistic modelling will be employed. The analyses are staged, with tests of the primary hypothesis (impact of the NRT intervention on 30-day abstinence rates at 6 months) as the first step and with step 2 involving tests of municipal- and individual-level factors predicted to explain the anticipated large impact of the NRT intervention in rural settings.

**Step 1:** Tests whether the provision of the NRT intervention impacts on 30-day abstinence rates. Experimental condition (participant randomly assigned to receive the NRT intervention package or to the control condition) is the categorical predictor in these analyses. Participants lost to follow-up will be assumed to be current smokers. As part of the step 1 analyses, we will also conduct a chi-square test to explore whether there is differential loss to follow-up between experimental conditions. Further we will replicate these analyses with all subjects with missing data excluded from the analyses. If the results are the same between the analyses where the missing data is excluded and where subjects lost to follow-up are assumed to still be current smokers, then we can safely assume that there is no differential attrition between conditions (or, at least none that impacted on the outcome of the trial). Finally, these analyses will be replicated with only those participants who provide *biochemically validation* of abstinence are coded as achieving abstinence at 6-month follow-up (all other participants are assumed to be current smokers).

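### Agreement between the missing-as-smoker and complete-case results cannot show that attrition was non-differential or harmless, so the Step 1 inference could certify a biased result

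*Protocol*

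**What the plan says.** Protocol, Analysis Plan, Step 1, handles missing outcomes in four moves.

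- Primary rule: "Participants lost to follow-up will be assumed to be current smokers".
- Check on loss rates: "we will also conduct a chi-square test to explore whether there is differential loss to follow-up between experimental conditions".
- Sensitivity analysis: "Further we will replicate these analyses with all subjects with missing data excluded from the analyses".
- Inference: if the two sets of results are the same, "then we can safely assume that there is no differential attrition between conditions". A parenthesis adds a fallback: at the least, any such attrition did not affect the trial's result.

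The text does not say what counts as the same: the same significance verdict, or similar odds ratios. Nor does it say which prevails if the chi-square test shows unequal loss while the two analyses agree.

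The planning figures are in Power calculations: "OR = 7.1; 6.7% 30-day abstinence rate at 6 months in those receiving NRT vs 1% in those not receiving the intervention", 20% attrition modelled as random, and "A sample of 290 participants per group (intervention versus control) is needed in order to obtain 80% power with 95% confidence interval".

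**The concern.** The inference treats two analyses of the same observed quitters as independent evidence on the people nobody observed. Missing-as-smoker divides the observed quitters by everyone randomised; complete-case divides the same quitters by those followed up. Neither contains information on the outcomes of the lost participants, so agreement between them cannot show whether quitters were lost at different rates in the two arms. The parenthetical fallback, that any differential attrition did not matter, fails for the same reason.

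What is at stake is how far the primary result can be trusted. The planned data are sparse: about 18 observed quitters in total and about 58 people missing per arm. Attrition is therefore a serious threat to the primary comparison, and this sentence is the protocol's stated ground for setting it aside.

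**Working it through.** **Inputs.** From Power calculations: 290 per arm, quit rates 6.7% and 1%, 20% attrition. From Randomization: 1:1 allocation. A two-sided 5% level is read from the 95% confidence interval. The split of loss by arm and the outcomes of the missing are not in the documents and are assumptions below.

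**The plan's own figure.** Odds ratio: (0.067/0.933)/(0.01/0.99) = 7.11, as stated. In 20,000 simulated trials with 290 per arm, 20% random loss, missing counted as smoking and a two-sided Wald logistic test, power was 81.1%. The stated 80% is reproduced. The trial simulations below use Pearson chi-square tests as a simple stand-in for the multilevel logistic model.

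**Step 1: what the comparison can measure.** Let a and b be the observed quitters in the intervention and control arms, n1 and n0 the numbers followed up, and N = 290.

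- Missing-as-smoker: OR = a(N − b) / [b(N − a)]
- Complete case: OR = a(n0 − b) / [b(n1 − a)]
- At low quit rates their ratio is about n1/n0 = (1 − intervention loss)/(1 − control loss)

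The ratio depends on how many were lost in each arm, not on who was lost.

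**Step 2: equal loss, different truths.** With 20% lost per arm, 232 are followed up in each. Observed quitters are 232 × 0.067 = 15.54 and 232 × 0.01 = 2.32. The two odds ratios are 7.02 and 7.11, and with equal loss the chi-square test gives p = 1. Those results stay the same whichever of these is true:

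- The missing quit at the rates of the observed: true OR 7.11.
- Missing controls quit at 6.7% and missing intervention participants at 0%: control (2.32 + 58 × 0.067)/290 = 2.14%, intervention 15.54/290 = 5.36%, true OR 2.59.
- Missing controls quit at 22.8% and missing intervention participants at 0%: both arms 5.36%, true OR 1.00.

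**Step 3: unequal loss unrelated to outcome.** With 10% lost in the intervention arm and 30% in the control arm, the expected odds ratios are 9.10 (missing-as-smoker) and 7.11 (complete case); 0.9/0.7 = 1.29, close to 9.10/7.11 = 1.28. Both are significant (Fisher p = 0.0006 and 0.0034 on rounded counts), while the loss difference has p = 1.7 × 10⁻⁹. Over simulated trials the two verdicts agree in about 95% at 10% vs 30% and about 90% at 30% vs 10%. The loss chi-square is significant in about 100% of both.

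**Step 4: outcome-related loss under a true null.** Assume 6.7% quit in both arms and 20% of non-quitters are lost in each arm. Only the loss among quitters varies.

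| Control quitters lost | Intervention quitters lost | Both analyses falsely favour NRT |
|---|---|---|
| 25% | 15% | about 5% |
| 30% | 10% | about 9% |
| 40% | 10% | about 17% |
| 50% | 10% | about 30% |
| 70% | 10% | about 67% |

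The nominal rate in that direction is 2.5%. The two analyses agree in 95-99% of trials across these rows. In the last row the loss chi-square flags about 22%. If total loss is instead held at 20% in each arm, with 70% vs 10% of quitters lost, both analyses are falsely significant in about 70% of trials and agree in 97%, and the chi-square flags 5%, its nominal rate.

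**Step 5: tipping counts.** Start from 15 or 16 intervention quitters and 2 or 3 control quitters, each out of 290, and add quitters among the missing controls with all missing intervention participants smoking. By Fisher or chi-square, p first exceeds 0.05 after 3 to 5 are added: 3/58 = 5% to 5/58 = 9%.

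**The case against.** The strongest replies, and what stands of each:

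- **Bias is not shown.** Correct. The documents give only 20% overall attrition. A reader might infer that the rule will certify a biased result; they support only that it could, if outcome-related loss differs by arm.
- **Agreement is not empty of information.** Correct on one reading. If the same means similar odds ratios, agreement does indicate similar loss proportions (Step 3 of the working). It still does not say who was lost. Only on the significance-verdict reading does it fail to show even equal loss.
- **The chi-square test covers unequal loss, and the parenthetical softens the claim.** Partly. With loss unrelated to outcome, the chi-square would expose the imbalance, and an unchanged verdict makes the parenthetical roughly right. Neither helps when loss is equal in size but different in kind.
- **The 70% vs 10% split is extreme.** Correct, and 6.7% quitting among controls is well above the planned 1%. At milder splits the false-positive rate is 5% to 30%. The 67% should not be read as typical.
- **The tipping counts are a one-sided worst case.** Correct. At the planned 1%, 58 missing controls would yield about 0.6 quitters, not 3 to 5.
- **Sensitivity analyses usually belong in the SAP.** Correct, and the SAP is not shown. The lack of a tipping-point analysis is not itself the point; the false inference in the protocol's own text is.

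**Conclusion.** The inference is invalid on either reading of sameness, and its parenthetical fallback does not rescue it. Agreement can occur in about 90-95% of trials with a 20-point difference in loss, and in 95-99% of trials when outcome-related loss raises the false-positive rate for NRT from a nominal 2.5% to between about 5% and 67%.

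Those ranges rest on assumed loss splits, a 6.7% quit rate in both arms for the null case, and chi-square tests in place of the multilevel model. They show what the rule would miss, not what this trial will experience.

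A reader might go further and conclude that the primary analysis is wrong or that the result will be biased. The documents do not support that: the sentence governs how robustness is interpreted and changes neither the missing-as-smoker estimate, the test, nor the sample size. This should be fixed, but it does not undermine the primary analysis itself.

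**What to change.** 1. Delete the sentence that infers an absence of differential or consequential attrition from agreement between the two analyses. Keep the complete-case analysis as a sensitivity analysis.
2. Report loss to follow-up by arm with the chi-square test already planned, and state that this test cannot detect informative loss occurring at equal rates.
3. Report with the primary result a tipping-point table that varies abstinence among missing participants separately by arm. It should include the number of missing controls who would have to be abstinent, with all missing intervention participants smoking, before the primary p-value exceeds 0.05, labelled as a one-sided worst case and set beside the control quit rate actually observed.

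The table could sit in the SAP; the deletion belongs in the protocol. The cost is one sentence removed and one table added, with no new data and no change to the sample size or primary analysis.

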## **Trial Protocol**

### **Scientific Abstract**

Quitting smoking is the most effective way of reducing the risk of cancer. One way of helping people stop smoking is to provide them with free Nicotine Replacement Therapy (NRT; e.g., nicotine patch), such as when NRT is sent to people by postal mail as part of a mass distribution initiative. Our previous research indicated that the impact of the mailed NRT intervention on increasing quit rates in rural areas may be substantial. The current research project seeks to confirm this finding and to understand the social determinants of health driving these anticipated large effects. This information is essential in order to target limited health resources to regions that are most in need, and who are likely to experience the greatest benefit.

Telephone numbers will be randomly selected from across rural regions of Canada in order to recruit adult smokers interested in completing a smoking survey and willing to be interviewed again in 6 months. The survey will ask participants about their smoking history, demographic characteristics, and a hypothetical question: would they be interested in receiving the nicotine patch if this were provided to them free of charge? Half of the smokers interested in receiving nicotine patches will be selected by chance and offered the NRT package. The other half of smokers will not be offered the nicotine patches. In addition, the municipality where each participant lives will be identified and participant data will be linked to relevant municipal characteristics (e.g., smoking rates, availability of health services). Characteristics of the participants and the municipalities in which they live will be used to explain why the nicotine patch intervention has a larger impact in some rural regions compared to others.

The findings from the proposed RCT are timely and of high relevance as the distribution of nicotine patches has substantial potential to combat the public health problem of cigarette related cancer, other diseases, and premature death from tobacco use. Targeting such tobacco cessation initiatives to rural regions may substantially increase the impact and cost-effectiveness of this intervention, helping to optimize the use of limited prevention resources while aiming to save the maximum number of lives.

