*Evidence for the benefits of providing free NRT by postal mail:* There are mass distribution initiatives of free NRT ongoing in several countries, including the US and Canada (Ontario). Further, there is evidence that the distribution of free NRT is **cost-effective**, with the cost of \$179 per participant in the Canadian mass distribution initiative. Moreover, a promising aspect about mass distribution of NRT initiatives is that, while it is available to everyone, **vulnerable populations (whether due to mobility issues, or co-existing mental health concerns) are by far the most likely to respond to the initiative and request free NRT.** An additional point as an argument of the benefit of providing free NRT is that it removes a financial barrier to access of NRT for people with low socioeconomic status, a factor that often co-occurs with areas of high smoking rates. Thus, the proposed tobacco cessation initiative is an excellent means of targeting vulnerable populations.

*Targeting NRT distribution to regions that may benefit most:* Results from our mailed nicotine patch trial indicated that the impact of free NRT distribution may be unexpectedly large in rural areas (OR = 9.59). This effect size is substantial in comparison to that observed in our earlier work on NRT distribution that largely comprised participants from urban/suburban regions (OR = 2.65). While encouraging, this large effect size requires replication to increase confidence in the results because the sample size of participants from rural regions in our earlier trial was small and this was a secondary analysis.

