**Step 2:** Tests to identify factors that systematically vary between individuals, and between municipalities, that explain the size of the impact of the NRT intervention on self-reported 30-day abstinence at 6-month follow-up. For these analyses, the data from urban comparison sample will be combined with the data collected in the current project of rural participants in order to allow for stronger tests. We have *pre-specified two hypothesized municipal factors* and predict that prevalence of smoking at the municipal level, and availability of health services in the municipality, will be related to the size of the impact of the NRT intervention. The multi-level logistic regression models constructed will include municipal-level sampling frame data (province or territory region of Canada), and municipal level smoking prevalence and health services availability data to determine the size of the impact of the intervention with the individual-level outcome data. Individual demographic (including participant gender) and severity of smoking characteristics will be included in order to identify individual-level factors relevant to the impact of the intervention.

*Secondary analyses* will add other characteristics of the municipality [average SES, population density, tobacco retailer density, NRT distributor (e.g., pharmacy, grocery store) density] to identify other contextual factors that may be important in determining the size of the impact of the NRT intervention. Additional secondary analyses will assess the effects of NRT and other predictors on relevant dependent measures pertaining to those who have not quit. These analyses will include multilevel models predicting the number of cigarettes smoked, intentions to quit, and whether participants have quit temporarily during a given time-period.

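### Moderation is modelled on the log-odds scale while the targeting aim is about extra quitters, so absolute gains should be reported beside the odds ratios

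*Protocol*

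**What the plan says.** The Scientific Abstract gives the purpose of targeting rural regions as "helping to optimize the use of limited prevention resources while aiming to save the maximum number of lives". The Background and the Discussion say much the same: direct scarce resources to the places where more people will stop smoking.

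The case that the rural effect is unusually large is made in the Background by setting an OR of 9.59 against the OR from earlier work that "largely comprised participants from urban/suburban regions (OR = 2.65"). No quit rates accompany the second figure, there or anywhere else in the protocol.

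The Power calculations paragraph gives the rural result with its rates, "OR = 9.59; 8.9% 30-day abstinence rate at 6 months in those receiving NRT vs 1% in those not receiving the intervention", and its precision, "n = 200 in participants from rural regions; 95% CI 1.19 to 77.16". The planning effect is "OR = 7.1; 6.7% 30-day abstinence rate at 6 months in those receiving NRT vs 1% in those not receiving the intervention".

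The Analysis Plan specifies multilevel logistic models for both steps. Step 2 seeks the factors that "explain the size of the impact of the NRT intervention on self-reported 30-day abstinence at 6-month follow-up". It pre-specifies two municipal moderators, smoking prevalence and availability of health services, and pools the new rural data with an urban comparison sample. It names no effect measure, so the scale on which moderation is judged follows from the model.

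**The concern.** Extra quitters per 100 smokers offered patches is an absolute quantity. A logistic model compares the effect between places as a ratio of odds ratios. The two agree on which place gains more when the control quit rate is the same everywhere, but not necessarily otherwise. At low control rates a given absolute gain produces a large odds ratio; at higher control rates the same gain produces a modest one.

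Step 2 compares municipalities that may differ in unaided quitting, and it pools two samples that may differ in the same way. Two errors are then possible. A moderator could look important although it makes no difference to the number of quitters. Or a moderator could look unimportant although patches add many more quitters at one end of its range. Either would feed straight into the advice on where to send patches, which is what the trial is for.

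**Working it through.** **Inputs.** From the Power calculations: 8.9% against 1% (OR 9.59, n = 200, 95% CI 1.19 to 77.16) and 6.7% against 1% (OR 7.1). From the Background: OR 2.65 for the mainly urban/suburban work. The control rate behind 2.65 is not in the protocol, so it is an assumption, shown below as a range.

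**Reproducing the protocol's figures.**
- The counts 9/101 and 1/99 are inferred from the stated n, rates and interval. They give OR = (9 × 98)/(92 × 1) = 9.59. The standard error of log OR is √(1/9 + 1/92 + 1/1 + 1/98) = 1.064, so the 95% CI is 1.19 to 77.16. This matches, and the control rate appears to rest on one quitter.
- Planning effect: (0.067/0.933)/(0.01/0.99) = 7.11, which matches 7.1.
- Absolute gains: 8.9 − 1 = 7.9 points (earlier rural result) and 6.7 − 1 = 5.7 points (planned).

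**Formulas.** With control rate p0 and odds o0 = p0/(1 − p0), the treated rate is p1 = OR·o0/(1 + OR·o0) and the gain is p1 − p0. In reverse, a gain d corresponds to OR = [(p0 + d)/(1 − p0 − d)]/o0.

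Example at p0 = 3.8%: o0 = 0.038/0.962 = 0.0395; 2.65 × 0.0395 = 0.1047; p1 = 0.1047/1.1047 = 9.5%; gain 5.7 points.

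| Assumed control rate | Gain if OR is 2.65 (points) | OR that equals a 5.7-point gain | OR that equals a 7.9-point gain |
|---|---|---|---|
| 1% | 1.6 | 7.11 | 9.67 |
| 2% | 3.1 | 4.09 | 5.38 |
| 3% | 4.6 | 3.08 | 3.96 |
| 3.8% | 5.7 | 2.66 | 3.35 |
| 5% | 7.2 | 2.28 | 2.81 |
| 5.5% | 7.9 | 2.17 | 2.66 |
| 10% | 12.7 | 1.68 | 1.96 |

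(The 9.67 in the first row differs from 9.59 only because it uses the rounded rates.)

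**Reading the table.** OR 2.65 delivers the planned rural gain at a control rate of about 3.8%, and the earlier rural gain at about 5.5%. Above those rates the setting with the smaller OR gains more quitters. Below them the rural gain is larger on both scales.

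**The opposite error.** Hold the OR at 7.1. The gain is 5.7 points at 1% control, 10.7 at 2% and 15.0 at 3%. A test of interaction in a logistic model would find no moderation here, although the gain in quitters differs by a factor of 15.0/5.7 = 2.6.

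**The case against.** The strongest reply is that the protocol is not confined to odds ratios. The primary hypothesis is worded in quit rates, the Power calculations give rates beside both rural odds ratios, and the planning effect seems to have been set on the rate scale (0.75 × 8.9% = 6.7%, whereas 0.75 × 9.59 = 7.19). A logistic model also yields predicted probabilities, and the statistical analysis plan, not shown here, may ask for them. This stands: the protocol does not rule out absolute summaries. What remains is that the moderation analysis is tied to a log-odds model, and the rural–urban contrast that motivates the trial is drawn in odds ratios alone.

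Three stronger readings are tempting and are not supported.

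- *The larger rural effect is only an artefact of a low control rate.* That needs a comparison control rate of about 3.8% to 5.5% or more, which the protocol neither gives nor excludes. The OR of 2.65 is also not purely urban.
- *The trial's own hypotheses imply that Step 2 will confirm moderation spuriously.* The health-services hypothesis says that help has more impact where services are scarce; it does not say that unaided quitting is lower there. For prevalence, the protocol argues that high-prevalence areas contain more smokers who want to quit. If that raises control quitting, an equal absolute gain gives a smaller OR there, against the hypothesis.
- *The risk difference would settle the rural–urban comparison where the OR cannot.* If the 20% lost to follow-up count as smokers, the planned rates become 5.36% and 0.8%, or about 15.5 and 2.3 quitters of 290. The OR is then 7.0 (95% CI 1.75 to 28.2), which includes 2.65. The risk difference is 4.6 points (1.8 to 7.3), which includes the gains implied by OR 2.65 at control rates of 2% to 5% (3.1 to 7.2). This is a matter of precision, which a change of scale does not cure. The protocol already concedes that the earlier estimate is unstable.

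**Conclusion.** The point holds in a limited form. The scale of the planned moderation analysis does not match the targeting question, and the two can give different answers when control quit rates vary. The discrepancy can be large: the same 5.7-point gain is an OR of 7.11 or 2.66 according to whether the control rate is 1% or 3.8%, and one OR of 7.1 covers gains from 5.7 to 15.0 points between 1% and 3%. Whether it will arise here is unknown, because it depends on control rates that the protocol does not report. The logistic models and the test of the primary hypothesis are sound as they are. This is a low-cost improvement to how effects are expressed and interpreted, not a fault that invalidates the design.

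**What to change.** Keep the logistic models and their tests, and add the following to the Analysis Plan.

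- **Step 1:** report the risk difference in 30-day abstinence with a 95% confidence interval beside the odds ratio.
- **Step 2:** for each of the two hypothesised moderators, pre-specify a low and a high value. From the fitted model, report standardised (marginal) predicted quit rates by condition at each value, the two risk differences, and the difference between them with a confidence interval, beside the interaction odds ratio.
- **Interpretation:** word statements about targeting from the absolute gains as well as the odds ratios, and do not call the rural effect larger than the urban one on the odds ratio alone. The absolute contrast need not be the sole condition for a targeting claim.

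The cost is a little more analysis from the same fitted models. The 290 per group, the data collection and the primary test are unchanged. The drawback is that, with very few control quitters expected, the absolute contrasts will be imprecise, and some moderation claims may come out weaker than on the odds-ratio scale.
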